### Data management {19}

All collected data will be stored and managed using a web-based data management system. Researchers are responsible for the data collection, especially for checking that all data related to this trial are filled out in the data manage system correctly and completely. A data management plan will be created beforehand for data validation.

### Confidentiality {27}

Personal data of the participants will be treated as confidential and stored securely during the whole course of this trial.

### Statistical analysis {20}

The primary and secondary endpoints will be analyzed according to the intention-to-treat principle. We will use descriptive statistical methods to measure patient characteristics and baseline clinical features. For primary and secondary outcomes, continuous variables will be presented as means ± standard deviations or median interquartile ranges (IQR). Categorical variables will be expressed as counts with percentages. We will use Student’s *T* tests or Mann–Whitney *U* tests to evaluate the differences between treatments in continuous variables according to normal distribution. Categorical variables will be compared using chi-squared or Fisher’s exact tests. All data collected will be analyzed by an independent statistical expert using SPSS (SPSS 22.0). A *p*-value < 0.05 will be considered statistically significant.

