#### Sample size calculation {14}

Based on previous studies [21], we set the non-inferiority cutoff at 5 mmHg. So, we assume that in the intervention group, PaCO_2_ may not elevate more than 5 mmHg after 24 h of the high-flow nasal cannula therapy with sequential noninvasive ventilation. According to previous studies, we also assume that the PaCO_2_ of intervention group is around 54 mmHg, and the control group is around 55 mmHg. Standard deviation is 9 mmHg, after 1:1 ratio randomization, and to assess non-inferiority using an *α* = 0.05, power = 0.80, and 1-side testing, 58 subjects were needed totally. Allowing for 10% loss to follow-up, we assume that we will need to recruit 70 patients. However, if loss to follow-up is greater than 10%, we aim to continue recruitment until 58 patients have a primary outcome recorded.

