Above all, no matter the clinical parameters or prognosis, HFNC may be noninferior to NIV. HFNC shows advantages in better patient comfort and tolerance, fewer complications, improved warming and humidification of their respiratory tracts, and better sputum excretion. However, if AECOPD patients are asleep, HFNC may increase the risk of CO_2_ retention and respiratory acidosis. On the other hand, NIV may face failure because of discomfort related to the ventilation and the mask, decreased secretion clearance, and patient–ventilator interaction mismatch.

This study aims to try to take advantage of both the strengths of HFNC and NIV to improve clinical care for AECOPD patients in the ED and critical care environments. We believe that the work of this trial will help us better understand whether HFNC with sequential NIV has any advantages over NIV alone. If this ventilatory strategy proves beneficial or non-inferior, it could provide crucial clinical evidence for improving care for AECOPD patients.

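### The trial is sized for non-inferiority with a 5 mmHg margin, but the stated primary analysis is an ordinary test of difference at p < 0.05, so the plan as written never tests non-inferiority

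*Protocol article*

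**What the plan says.** **Sizing.** Sample size calculation {14} states: "Based on previous studies [21], we set the non-inferiority cutoff at 5 mmHg". It assumes that PaCO2 in the "intervention group is around 54 mmHg, and the control group is around 55 mmHg", and adds "Standard deviation is 9 mmHg, after 1:1 ratio randomization". The result is given as follows: "to assess non-inferiority using an *α* = 0.05, power = 0.80, and 1-side testing, 58 subjects were needed totally".

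**Meaning given to the margin.** The same section explains the cutoff by saying that PaCO2 in the intervention group "may not elevate more than 5 mmHg after 24 h of the high-flow nasal cannula therapy with sequential noninvasive ventilation".

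**Analysis.** Statistical analysis {20} covers primary and secondary endpoints in one paragraph. Continuous variables get Student's t or Mann–Whitney U "tests to evaluate the differences between treatments in continuous variables according to normal distribution", and a p-value under 0.05 counts as significant. It mentions no margin, shifted null hypothesis, confidence interval or sidedness.

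**Intended conclusion.** The Discussion looks ahead to the case "If this ventilatory strategy proves beneficial or non-inferior".

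The abstract, Objectives {7} and Outcomes {12} mention neither non-inferiority nor the margin.

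**The concern.** The sizing and the analysis test different hypotheses. The sample size is built to reject the null that the intervention is worse by 5 mmHg or more. The stated analysis tests the null of no difference. Failing to reject no difference is not evidence of non-inferiority, because an imprecise trial fails to reject it whatever the truth is. A standard Mann–Whitney p-value is further from the target still, since it says nothing about a 5 mmHg margin on a mean difference.

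Two secondary points add to this. The explanation of the margin reads as a within-arm rule: the intervention group's own PaCO2 must not rise by more than 5 mmHg. Also, p < 0.05 with no stated side does not clearly carry over the one-sided 5% used for sizing.

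At stake is the primary conclusion. Followed literally, the analysis cannot deliver the claim the trial was sized for. The likely substitute, reading a non-significant difference as non-inferiority, has a false-claim rate far above 5%.

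**Working it through.** **Inputs, all from Sample size calculation {14}:** margin M = 5 mmHg; assumed means 54 (intervention) and 55 (control), so true difference δ = −1 mmHg; SD σ = 9 mmHg; 1:1 allocation; one-sided α = 0.05; power 0.80; 58 evaluable patients, or 29 per arm. Differences are intervention minus control, so positive values mean the intervention is worse.

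**1. Reproduce the 58.**
- Normal approximation: n per arm = 2σ²(z₀.₉₅ + z₀.₈₀)² / (M − δ)² = 2 × 81 × (1.645 + 0.842)² / 6² ≈ 27.8. This rounds up to 28 per arm, 56 in total.
- Exact noncentral t: 29 per arm, 58 in total, with power 80.6%.

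The stated figure is therefore a between-arm non-inferiority calculation at one-sided 5%, with an effective distance of 5 + 1 = 6 mmHg.

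**2. Compare the two decision rules at 29 per arm.** SE = 9 × √(2/29) = 2.364 mmHg, with 56 degrees of freedom.
- Non-inferiority rule (one-sided 95% upper bound below 5): the half-width is t₀.₉₅ × SE = 3.95, so the observed difference must be below 5 − 3.95 = 1.05 mmHg.
- Difference test (two-sided p ≥ 0.05): the half-width is t₀.₉₇₅ × SE = 4.73, so any observed difference smaller than 4.73 mmHg is non-significant.

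An observed deficit between 1.05 and 4.73 mmHg fails the non-inferiority criterion but is non-significant on the stated test.

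**3. Non-significance when the true deficit is 5 mmHg.** The noncentrality is 5 / 2.364 = 2.115.

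| Evaluable per arm | P(two-sided p ≥ 0.05) |
|---|---|
| 29 (58 in total) | 45% |
| 33 (66, the abstract's enrolment, all evaluable) | 40% |
| 35 (70, the recruitment target, all evaluable) | 37% |

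If the difference test is one-sided at 5%, its power at 29 per arm is 67.2%, so non-significance occurs in 100 − 67.2 = 32.8% of trials. Every figure is far above 5%.

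**4. Power of the difference test for the assumed 1 mmHg benefit.** At 29 per arm it is 7.0% two-sided and 11.0% one-sided. Reaching 80% (two-sided) would need 2 × 81 × (1.960 + 0.842)² / 1² ≈ 1,272 per arm, or 2,544 in total. A non-significant result is thus the expected outcome even if every planning assumption is right.

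**5. If p < 0.05 is applied as a two-sided 95% interval against the margin.** The noncentrality is 6 / 2.364 = 2.54, and power at one-sided 2.5% is 70.4% instead of the stated 80%. Restoring 80% would need 72 (normal) to 74 (exact t) evaluable patients.

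**6. The within-arm wording.** Eligibility {10} requires PaCO2 of at least 55 mmHg at entry. An intervention arm with no improvement has a rise of 0, which is below 5, so it would satisfy the sentence as written however much the control arm improved. Step 1 shows that the sizing did not use this reading.

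**The case against.** The strongest reply is that the two sections can be read together. The sample size section already supplies the hypothesis, margin, alpha and side, while the analysis section is a generic paragraph naming a family of tests, and a t-test can be run against a null shifted by 5 mmHg. On this view the exact confidence bound and the order of testing belong in an SAP that is not shown.

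This does not remove the problem. The analysis section expressly includes the primary endpoint, describes testing differences between treatments, and sets its own significance threshold. That is a stated rule for a different null hypothesis, not a detail deferred to another document. Nothing in the text shifts the null, and the Mann–Whitney option as written has no connection to the margin.

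Several narrower points do stand:
- The 45% is not the error rate of a rule the protocol states. It applies only if p ≥ 0.05 is taken as non-inferiority.
- The analysis section gives no side for p < 0.05, so it is unclear rather than openly contradictory on this point. The 70% applies only if a two-sided 95% interval is used.
- The within-arm sentence is probably loose wording, because 58 is recovered only with a between-arm margin.
- A rank-based shift estimate with a confidence limit could be set against a margin. The protocol does not propose one, and it would not in general estimate the mean difference named as the primary endpoint.

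**Conclusion.** The concern holds. The plan contradicts itself on its primary question: it is sized to exclude a 5 mmHg deficit and hopes to conclude non-inferiority, but the analysis it fixes tests only for a difference. No section gives a rule for declaring non-inferiority. If non-significance were used in its place, the false-claim rate at the margin would be about 45% with 58 evaluable patients (33% for a one-sided difference test), against a planned 5%.

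The figures assume SD 9 mmHg, normally distributed data and 29 per arm. The protocol gives that SD beside 24 h PaCO2 levels, and it is applied here to the change from baseline; a different SD of change would move the percentages. The mismatch between hypothesis and test depends on none of these assumptions. The sample size of 58 is not in error; the analysis has to be brought into line with it.

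**What to change.** - **Statistical analysis {20}:** state that the primary analysis estimates the between-group mean difference (intervention minus control) in PaCO2 change from baseline to 24 h, with a one-sided 95% upper confidence bound (the upper limit of the two-sided 90% interval). Declare non-inferiority only if that bound is below +5 mmHg. Test superiority only once non-inferiority is shown. Do not use a Mann–Whitney p-value for the primary endpoint; keep the ordinary difference tests for secondary endpoints.
- **Sample size calculation {14}:** reword the margin as a between-group difference in place of a limit on the rise within the intervention arm.
- **Abstract, Objectives {7} and Outcomes {12}:** name the non-inferiority hypothesis and the margin.
- **If a two-sided 95% interval is preferred:** restate power as about 70% at 58 evaluable patients, or plan for 72 to 74.

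The same wording should go into the SAP, and the rule should be fixed before outcome data by arm are examined. The recommended version changes wording only. It needs no extra patients, visits or data, and retains 80.6% power at 58 under the protocol's own assumptions.

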### Interventions

#### Intervention description {11a}

In the intervention group, patients will receive HFNC when they are awake in daytime and early evening hours. When they are asleep or at night between 10 pm and 6 am, these patients will change to NIV. The HFNC group will be given a flow rate of 60 L/min and a temperature of 37° C [17]. If a patient is not tolerating these settings, flow rate and temperature will be titrated to the maximum tolerated level, but with a minimum flow rate of 30 L/min.

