#### Outcomes {12}

The primary endpoint is the mean difference in PaCO_2_ from baseline to 24 h after randomization. Secondary endpoints include the following: (1) the mean difference in PaCO_2_ from baseline to 6, 12, and 18 h after randomization; (2) dyspnea score at 6, 12, 18, and 24 h; (3) overall discomfort score related to the ventilatory strategy and proportion of patients showing poor tolerance to treatment at 24 h (e.g., complaining about noise, pressure, temperature, gastric distension, vomiting, or claustrophobia); (4) the proportion of patients who change treatment strategies (switch to the other ventilatory strategy or to no support); (5) rate of treatment failure, defined as the proportion of patients who had PaCO_2_ worsening or reduction < 10 mmHg from baseline, or worsening with no improvement of the dyspnea or respiratory rate > 30 breaths per minute; (6) respiratory rate; (7) rate of endotracheal intubation within 24 h; (8) length of hospital stay; and (9) all-cause mortality.

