### Data collection and measurement {18}

We will collect patient personal and baseline clinical characteristics as delineated above (e.g., age, gender, RASS, etc.). Furthermore, we will collect vital signs, systolic and diastolic pressure, heart rate, peripheral oxygen saturation, the presence of dyspnea based on the Borg dyspnea scale (score from 0 to 10 after 6 min’ walk, 0 means no dyspnea, 10 means the maximum), the arterial blood gas at inclusion, and starting time and settings for HFNC/NIV at 6, 12, 18, and 24 h. During the study intervention, patients will have continuous SpO_2_, electrocardiogram, respiratory rate, and noninvasive blood pressure monitoring. All relevant variables and endpoints will be evaluated at 6, 12, 18, and 24 h after randomization. In particular, we will record the NIV and HFNC settings as well as the proportion of patients who change treatment modality during the study period (i.e., switch to the other ventilatory strategy or to no ventilatory support). The discomfort score related to different ventilatory strategies will also be assessed at the established time points, and the proportion of patients showing poor tolerance to the treatment but who do not interrupt or withdrawal due to noise, temperature of flow, gastric distension, vomiting, or claustrophobia will be recorded. We will also record the rate of treatment failure due to a worsening PaCO_2_, a less than 10 mmHg reduction in PaCO_2_ from baseline, a worsening or lack of improvement in dyspnea, or a respiratory rate > 30 breaths per minute. Hospital length of stay and any-cause in-hospital mortality will all be collected. The main schedule of enrolment, intervention, and assessment were listed in the Table 1.

**Table 1 Tab1:** Schedule of enrolment, intervention, and assessment

Time point	Study period						
	Enrollment	Allocation	Post-allocation				
			Start	6 h	12 h	18 h	24 h
Enrollment							
Eligibility	** × **						
Informed consent	** × **						
Allocation		** × **					
Intervention							
Intervention group			** × **	** × **	** × **	** × **	** × **
Control group			** × **	** × **	** × **	** × **	** × **
Assessment							
Patient characteristics	** × **						
Vital signs	** × **		** × **	** × **	** × **	** × **	** × **
Medical history	** × **						
Laboratory results							
ABG			** × **	** × **	** × **	** × **	** × **
RASS score			** × **	** × **	** × **	** × **	** × **
Borg Dyspnea score			** × **				** × **
Discomfort score			** × **				** × **

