### Methods in analysis to handle protocol non-adherence and any statistical methods to handle missing data {20c}

All efforts will be made to complete the follow-up and data collection and avoid missing data. Analyses will be conducted in complete cases. We will also perform sensitivity analyses by imputing the missing data to worst cases.

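### Separate unadjusted tests of PaCO2 change at 6, 12, 18 and 24 h are valid, but they give up precision and leave the 24 h course without a summary; one baseline-adjusted repeated-measures model would use the data better

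*Protocol article*

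**What the plan says.** Outcomes {12} sets a single-time primary endpoint: "The primary endpoint is the mean difference in PaCO_2_ from baseline to 24 h after randomization". The first secondary endpoint is "the mean difference in PaCO_2_ from baseline to 6, 12, and 18 h after randomization", and respiratory rate is a further secondary endpoint.

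Data collection and measurement {18} states: "All relevant variables and endpoints will be evaluated at 6, 12, 18, and 24 h after randomization". Table 1 marks blood gases and vital signs at the start and at each of those four times.

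Statistical analysis {20} names one approach for continuous variables: Student's t or Mann–Whitney U "tests to evaluate the differences between treatments in continuous variables according to normal distribution". It mentions no adjustment for baseline, no repeated-measures model and no measure averaged over time. On missing data, section {20c} says "Analyses will be conducted in complete cases", with worst-case imputation as a sensitivity analysis.

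The intervention arm changes device within the 24 h. Patients receive HFNC while awake by day and in the early evening, and: "When they are asleep or at night between 10 pm and 6 am, these patients will change to NIV".

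**The concern.** Each patient supplies a baseline gas and four later gases, but the plan reads the later gases one at a time, each as a change score compared between arms.

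Three things are lost:

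- **Use of baseline.** A test on the change subtracts baseline with a fixed weight of one. Regression on baseline estimates the weight and, apart from the small cost of estimating it, is never less precise.
- **Partly observed patients.** In complete-case testing, a patient without a gas at one time contributes nothing at that time, although the other gases carry information about it.
- **A summary over the day.** No clock time for randomization is fixed, so a gas at a given hour may be drawn on HFNC in one intervention patient and on NIV in another. The course of the arm difference over the day is therefore of interest. Four separate results may disagree, and the plan does not say how to read them together.

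At stake is the width of the intervals in a small trial and the clarity of the secondary PaCO2 and respiratory-rate results. The validity of the primary comparison is not at stake.

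**Working it through.** **Inputs.** From Sample size calculation {14}: margin 5 mmHg, assumed means 54 (intervention) and 55 (control), SD 9, one-sided α 0.05, power 0.80, total 58 (29 per arm). The within-patient correlation is not given. It is assumed here, mainly between 0.6 and 0.9.

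**1. The plan's own figure.** The distance from the assumed difference to the margin is 5 + 1 = 6 mmHg. The normal approximation gives 2 × (1.645 + 0.842)² × 81/36 = 27.8, so 28 per arm or 56 in total. The noncentral-t calculation gives power 0.793 at 28 per arm and 0.806 at 29 per arm, hence 58. The stated figure is reproduced, and it matches a single-time two-sample comparison.

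**2. Repeated measures alone, complete data.** A model with a separate mean for each arm and time, unstructured covariance and no baseline term gives the same 24 h contrast as the t-test. In a simulated example the estimate was 2.262 and the SE 2.286 both ways. Any gain at a single time must therefore come from baseline adjustment or from missing gases.

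**3. Gain from baseline adjustment.** Let r be the correlation between baseline and the 24 h gas, with SD 9 at both times.

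- Change test: SE = 9√(2/29) × √(2(1 − r)) = 2.363 × √(2(1 − r))
- Baseline-adjusted: SE = 2.363 × √(1 − r²), ignoring the small cost of estimating the slope
- Ratio: √((1 + r)/2)

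| Assumed correlation | r at 24 h | SE, change | SE, adjusted | Reduction |
|---|---|---|---|---|
| Equal, 0.6 | 0.6 | 2.11 | 1.89 | 11% |
| Equal, 0.9 | 0.9 | 1.06 | 1.03 | 3% |
| Decaying, 0.6 per 6 h step | 0.6⁴ = 0.130 | 3.12 | 2.34 | 25% |
| Decaying, 0.9 per 6 h step | 0.9⁴ = 0.656 | 1.96 | 1.78 | 9% |

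The same ratio applies at 6, 12 and 18 h, with r taken as the correlation of that gas with baseline. The percentage does not depend on the SD of 9, only on the SDs being equal at the two times. With unequal SDs s₀ (baseline) and s₁, the variance saved per patient is (s₀ − r·s₁)², which is never negative but can be close to zero.

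**4. Gain from missing 24 h gases.** Simulation with 33 per arm, 10% of 24 h gases missing at random and decaying correlation compared a baseline-adjusted completer analysis with the joint model. The SEs were 2.314 against 2.282 (0.6), 2.157 against 2.104 (0.8) and 1.837 against 1.757 (0.9). These are reductions of about 1%, 2% and 4%.

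**5. The averaged change is a different quantity.** Under equal correlation ρ, the variance of the mean of the four changes is [(1 + 3ρ)/4 + 1 − 2ρ]·SD² = 1.25(1 − ρ)·SD². A single change has variance 2(1 − ρ)·SD², so the ratio is 0.625. With decaying correlation of 0.6, 0.8 and 0.9, the ratio is 0.54, 0.50 and 0.48 against the 24 h change, but 1.17, 1.48 and 1.67 against the 6 h change. The average is then less precise than the planned 6 h comparison.

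**The case against.** The best defence is that nothing here is wrong. The times are listed as separate endpoints and tested separately, which is consistent. The sample size matches the planned test. If loss exceeds 10%, recruitment is meant to continue until 58 patients have a primary outcome, which protects the primary comparison from missing gases. A joint model assumes data are missing at random, and that is doubtful if gases are missing after deterioration or withdrawal. Covariance structure and an extra averaged estimate are matters commonly left to an analysis plan, which is not shown.

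Most of this stands and limits the point. It does not remove it, because Statistical analysis {20} does not leave the method open: it names unadjusted two-sample tests for continuous outcomes, and complete cases are fixed elsewhere. A more precise method is available from the same data.

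A reader might draw three stronger conclusions that the document does not support:

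- **That no analysis estimates the strategy's effect over 24 h.** The primary endpoint does estimate the net change after 24 h, when each patient is back at the clock time of randomization. Only a time-averaged or longitudinal estimate is absent.
- **That separate tests wrongly ignore within-patient correlation.** Each test compares independent patients at one time, so no independence assumption is broken.
- **That single-time testing costs 60% more patients (1/0.625 = 1.6).** That ratio sets an averaged estimand against a single-time one and holds at every ρ only under equal correlation. It is not precision lost on any planned endpoint.

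**Conclusion.** The point holds as one of efficiency and reporting. The planned tests are valid, and the 24 h primary endpoint and the 58 patients stand. Against the unadjusted test on change, a baseline-adjusted model would reduce the SE of the 24 h contrast by about 3% to 11% under equal correlation of 0.9 to 0.6, and by about 9% to 25% if those correlations apply per 6 h step and decay. Using earlier gases where the 24 h gas is missing adds about 1 to 4%.

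These sizes rest on assumed correlations and on equal SDs at baseline and 24 h. Eligibility requires PaCO2 of at least 55 mmHg, which may narrow the baseline spread, so the trial's own gain could differ. The averaged arm difference adds a readable summary of the day; its precision relative to a single time depends on the correlation pattern and should not be advertised as a sample-size saving.

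**What to change.** In Statistical analysis {20}, keep the 24 h contrast as primary and replace the separate PaCO2 tests with one linear mixed model for repeated measures:

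- **Terms:** arm, time, arm-by-time, baseline PaCO2 and baseline-by-time.
- **Covariance:** unstructured, with a simpler structure named in advance as fallback, and Satterthwaite degrees of freedom.
- **Report:** the 24 h, 6 h, 12 h and 18 h contrasts with confidence intervals from the same fit. For the 24 h contrast, judge the interval against the 5 mmHg margin at the α used in the sample size calculation.
- **Add:** the arm difference averaged over 6 to 24 h with its confidence interval, labelled as a supportive secondary estimate.
- **Respiratory rate:** use the same model with its own baseline.
- **Missing data:** keep the worst-case sensitivity analysis, because the model assumes data are missing at random.

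The cost is a few sentences and slightly more programming; SPSS, already named, fits such models through its MIXED procedure. No patients or measurements are added. The one real drawback is estimating a 4 × 4 covariance matrix from about 58 patients, which is why the fallback should be fixed beforehand.

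### The trial is sized for non-inferiority with a 5 mmHg margin, but the stated primary analysis is a difference test at p < 0.05 that ignores the margin

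*Protocol article*

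**What the plan says.** Three places in the protocol article bear on this point.

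- **Sample size calculation {14}** sets the hypothesis. It states "we set the non-inferiority cutoff at 5 mmHg", takes the view that PaCO2 in the "intervention group is around 54 mmHg, and the control group is around 55 mmHg", adds "Standard deviation is 9 mmHg, after 1:1 ratio randomization", and sets out "to assess non-inferiority using an *α* = 0.05" with 80% power and one-sided testing. The result is that "58 subjects were needed totally".
- **Statistical analysis {20}** sets the test. It addresses primary and secondary outcomes together, summarises continuous variables by mean and SD or median and IQR, and applies Student's t or Mann–Whitney U tests "to evaluate the differences between treatments in continuous variables according to normal distribution". The criterion is a p-value "< 0.05 will be considered statistically significant".
- **Discussion** sets out the conclusion hoped for: "If this ventilatory strategy proves beneficial or non-inferior".

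No other section says how the 24 h PaCO2 result is to be compared with 5 mmHg.

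**The concern.** A non-inferiority claim needs evidence that the intervention is not worse by as much as the margin. A test of whether the arms differ addresses another null hypothesis. Its p-value does not depend on the margin, and a large p can mean either that the arms are alike or that the data are too noisy to tell them apart.

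Two things are at stake. First, the stated rule gives almost no route to the intended conclusion under the protocol's own assumptions, because the expected advantage is only 1 mmHg. Second, the stated rule invites reading p ≥ 0.05 as no difference and hence non-inferior. That error is anti-conservative, and it grows with noise: the less precise the trial, the easier it is to pass.

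**Working it through.** **Inputs, all from Sample size calculation {14}:** margin 5 mmHg; assumed means 54 (intervention) and 55 (control), so a true difference d (intervention minus control, positive = worse) of −1 mmHg; SD 9 mmHg; 1:1 allocation; one-sided alpha 0.05; power 0.80; 58 evaluable, i.e. n = 29 per arm. SD 9 is applied to the primary endpoint, since the protocol gives no other SD.

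**Standard error.** SE = SD × √(2/n) = 9 × √(2/29) = 2.3635 mmHg, with 56 degrees of freedom. The t quantiles are 1.6725 (one-sided 0.05) and 2.0032 (two-sided 0.05). Power figures use the noncentral t distribution.

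**Step 1: reproduce 58.** For a test against the margin, the noncentrality is (5 − (−1))/SE = 6/2.3635 = 2.54.
- 29 per arm: power 80.6% at one-sided 0.05.
- 28 per arm: power 79.3%.

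So 29 per arm, 58 in total, is the smallest size reaching 80%. The stated figure reproduces exactly as a margin-based test. The normal approximation gives 56. A two-sided 0.05 difference test would need 1,272 per arm to detect 1 mmHg with 80% power.

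**Step 2: what the difference test delivers at the planned effect.** At d = −1, noncentrality is −1/2.3635 = −0.42. The probability of two-sided p < 0.05 in favour of the intervention is 6.1%.

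**Step 3: what happens if p ≥ 0.05 is read as non-inferior.** At d = +5, exactly on the margin, noncentrality for n = 29 is 5/2.3635 = 2.12.

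| Evaluable per arm | P(p ≥ 0.05) when truly 5 mmHg worse | Planned false non-inferiority rate |
|---|---|---|
| 29 | 45.3% | 5% |
| 33 | 39.6% | 5% |
| 35 | 37.0% | 5% |

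The rows for 33 and 35 per arm correspond to totals of 66 (Abstract) and 70 ({14}) with no losses. With 29 per arm and a true deficit of 6 mmHg, the figure is still 29.6%.

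**Step 4: the same in observed differences (29 per arm, SD 9).**
- Difference test: not significant for observed deficits up to 2.0032 × 2.3635 = 4.73 mmHg.
- One-sided 95% upper bound at that deficit: 4.73 + 1.6725 × 2.3635 = 4.73 + 3.95 ≈ 8.69 mmHg, well beyond the margin.
- Margin-based test: met only if the observed difference is below 5 − 3.95 = 1.05 mmHg.

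Observed deficits between about 1.05 and 4.73 mmHg are therefore non-significant and yet fail the non-inferiority criterion.

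**Step 5: sensitivity to the SD.** The SD of the change may differ from 9. Taking 6 and 12 mmHg as illustrative assumptions, with 29 per arm, SE is 1.576 and 3.151. The probability in Step 3 becomes 12% and 66%. More noise makes the misreading easier, as expected of a test used the wrong way round.

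**Step 6: sensitivity to sidedness.** {20} does not state sidedness. With one-sided 0.05 tests at SD 9, significance for benefit at d = −1 occurs in about 11% of trials, and a test for harm at d = +5 is non-significant in about 33%. The conclusion does not change.

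**The case against.** The best defence is that {20} never writes down a null value. A t test can be run against a shifted null, and the 0.05 threshold matches the alpha in {14}, so the two sections could be read together as a one-sided test against 5 mmHg with the rule left to an analysis plan not shown here. This reading does not fit the text. One generic sentence governs every continuous outcome, only the primary endpoint has a margin, and a Mann–Whitney p-value as described gives nothing in mmHg to compare with 5. Silence could be left to an analysis plan. Here the protocol names a test and a threshold, and an analysis plan with a margin-based rule would have to depart from them.

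Four narrower objections have force:

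- A significant result in favour of the intervention would also exclude +5 mmHg, so the difference test is not wholly unable to support non-inferiority. Under the planned assumptions that happens in about 6% of trials.
- The 45% applies only if a non-significant result is taken as non-inferiority. The protocol does not say it will be, but it also offers no other criterion and does not rule this out.
- The means of 54 and 55 mmHg look like levels at 24 h, whereas Outcomes {12} defines the endpoint as change from baseline. The figures are conditional on SD 9 for the change.
- {14} also words the margin as a rise within the intervention group. The arithmetic reproduces 58 only with a between-arm margin, so that is the reading used here, but the text should say so.

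**Conclusion.** The concern holds. {14} and {20} fix different hypotheses for the same primary endpoint, and the one in {20} does not answer the question for which 58 patients were calculated. Assuming 29 evaluable per arm, SD 9 mmHg for the endpoint and a two-sided test, the stated analysis has about a 6% chance of a significant result in favour of the intervention at the planned effect, against about 81% for the margin-based test. If non-significance is taken as success, the false non-inferiority rate at the margin is about 45% (37% with 35 per arm) instead of 5%. The exact figures move with the SD and sidedness; the mismatch does not. Because it affects the primary endpoint and the headline conclusion, it must be corrected before the data are analysed.

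**What to change.** In Statistical analysis {20}, give the primary endpoint its own rule, for example:

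*The between-arm difference (intervention minus control) in PaCO2 change from baseline to 24 h will be estimated with a two-sided 90% confidence interval, matching the one-sided alpha of 0.05 in {14}. Non-inferiority will be concluded only if the upper limit is below 5 mmHg. Superiority will be tested at two-sided 0.05 only once non-inferiority is shown. A non-significant difference test will not be reported as non-inferiority.*

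If a rank-based method is kept for non-normal data, the same rule can be applied to a Hodges–Lehmann estimate with its 90% interval. {14} should state that the 5 mmHg is a between-arm margin. The p < 0.05 difference tests can stay for the secondary endpoints.

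**Cost.** A few sentences, with no new data and no more patients: 58 evaluable patients give 80.6% power under this rule. A merely non-significant result can no longer be presented as success. If a 95% interval (one-sided 0.025) is preferred, power with 58 is about 70% and should be restated in {14}; 80% would then need 37 per arm, 74 evaluable in total.
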